### Additional file 1: Statistical analysis plan

[name], [name]

Version 19^th^ May 2015

1. **Preamble**

This plan was developed to analyse data from the SEICK (Safe and Effective Iron for Children in Kenya) trial. The study received ethical clearance in Kenya (Kenyatta University National Hospital/University of Nairobi, #KNH-ERC/A/402)) and in England (London School of Hygiene and Tropical Medicine, #6503)), and was registered at ClinicalTrials.gov (NCT02073149). The principal features of the planned analysis were established as part of the trial proposal. The current plan provides an update, was finalised after data collection but before breaking the randomization code, and should take precedence over the trial proposal.

1. **Trial objectives**

The study was primarily conceived to assess non-inferiority of daily home fortification with 3mg iron as NaFeEDTA compared with 12.5 mg iron as encapsulated ferrous fumarate, with haemoglobin concentration at the end of the 30-day intervention period as the primary outcome.

The study proposal states the following objectives:

1. In children aged 12-36 months, to compare daily home fortification for 30 days with two iron formulations (3mg iron as NaFeEDTA versus 12.5 mg iron as encapsulated ferrous fumarate) regarding:
2. Haemoglobin concentration at the end of the 30-day fortification period ***(primary objective)***;
3. Iron status at the end of the fortification period;
4. Serum NTBI concentrations at 3 hours after ingesting the first fortificant dose;
5. Faecal calprotectin concentration at the end of the fortification period;
6. *P. falciparum* infection at the end of the fortification period as indicated by whole blood density of asexual parasites or the presence of antigenemia;
7. Adherence to intervention.
8. To compare daily home fortification for 30 days with iron (3mg iron as NaFeEDTA or 12.5 mg iron as encapsulated ferrous fumarate) versus placebo regarding:
   1. The indicators listed under objective 1a-f;
   2. Time to development of anaemia after cessation of iron fortification.
9. To evaluate the accuracy of self-reported adherence with home fortification, using medication events monitoring system as a gold standard.
10. To assess associations between major intestinal parasites and haemoglobin concentration at baseline.
11. To compare intervention effects of iron on intestinal biota.

Objectives 1c, 1d, 4 and 5 are conditional to sufficient resources still being found to conduct the laboratory analyses required, and will not be further discussed in this plan.

1. **Study type and key design features**

The study concerns an individually-randomised, controlled non-inferiority trial with three parallel arms, with participants randomised to daily home fortification for 30 days with sachets containing either a) 3 mg iron as NaFeEDTA (experimental treatment); b) 12.5 mg iron as encapsulated ferrous fumarate (positive control); or c) placebo (negative control).

Demonstration of non-inferiority in a trial with two arms can have two meanings only: both interventions are equally effective, or both interventions are equally ineffective against placebo. Thus, as per guidelines of the European Medicine Agency [1] and the International Conference on Harmonisation of Technical Requirements for Registration of Pharmaceuticals for Human Use [2], we included a third arm with placebo, which allows a) demonstration of superiority of home fortification with 3mg iron as NaFeEDTA over placebo (proof of efficacy); b) demonstration of superiority of the reference (12.5 mg iron as encapsulated ferrous fumarate) over placebo (proof of assay sensitivity); and c) demonstration that the home fortification with 3mg iron as NaFeEDTA retains most of the efficacy of the reference over placebo (proof of non-inferiority).

Haemoglobin concentration at baseline was strongly expected to be prognostic for haemoglobin concentration at the end of intervention. To achieve group balance in size and baseline haemoglobin concentration, randomisation was based on a stratified block design, with strata defined by baseline haemoglobin concentration class (<100 g/L and ≥100 g/L) and randomly sized permuted blocks of 6 or 9. Stratification at the stage of randomisation and adjustment for this stratification in the analysis was also expected to improve the efficiency of the analysis and the precision of the estimated intervention effect. Because of the short recruitment period, we did not expect blocks to be associated with haemoglobin concentration, even though we could not entirely exclude this possibility (e.g. due to seasonal changes in diet or malaria transmission). We did not conduct interim analyses and had no stopping guidelines.

**Figure S1:** **Summary of study design (not to scale)**.

1. **Sample size calculations**

The target sample size was 108 participants per group, which was determined using procedures and terminology for sample size calculations in non-inferiority trials as recommended by US Food and Drug Administration [3,4]

1. Based on a meta-analysis [5], we estimated the effect of 12.5 mg ferrous fumarate on haemoglobin concentration relative to placebo. The lower limit of the 95% CI thus obtained (9.3 g/L) was used as M_1_, the minimum anticipated effect of 12.5 mg ferrous fumarate in our trial (**Figure 2;** left panel).
2. Next, we set M_2_ as the margin specified to preserve 50% of the anticipated minimum effect of 12.5 mg ferrous fumarate anticipated reduction in the 3mg NafeEDTA test treatment. This margin (haemoglobin concentration of 4.7 g/L) can be interpreted as the largest loss of effect compared to 12.5 mg ferrous fumarate (inferiority) that would be acceptable, and also is below an effect for 5g/L haemoglobin concentration that we consider to be of minimum importance for public health.
3. We set the sample size so that the lower limit of the 95% CI around the difference in haemoglobin concentration between the two iron formulations (i.e. 12.5 mg ferrous fumarate and 3.0 mg iron as NaFeEDTA) would lie above M2 (Figure 1; right panel).

Peer reviewers or editors of scientific journals may demand that we report sample size calculations and statistical power. Although such calculations are critically important in planning a study, we consider statistical power to be an exclusively pre-trial concept, which is irrelevant and conceptually wrong in the interpretation of study results, based on assumptions that are not usually met during trial implementation, and prone to be misinterpreted by most readers [6,7]. Thus we intend to refrain from reporting sample size calculations, but we will report the method used to determine the non-inferiority margin.

[figure not shown]

Figure S2: Theoretical framework for sample size determination

1. **Software**

Anthropometric indices will be calculated using WHO Anthro software vs.3.2.2 (World Health Organisation, Geneva, Switzerland). Data will be double entered, checked for completeness and verified for possible entry errors using Microsoft Excel. Data cleaning and analysis will be done using SPSS 21 (IBM, Armonk, NY); R-software version 3.2.0 ([www.r-project.org](http://www.r-project.org)) and CIA 2.2.0 (<http://www.som.soton.ac.uk/research/sites/cia/>and PowerView vs.3.5.2 (AARDEX Group ltd, Sion Switzerland) to analyse electronic adherence data.

1. **Intention-to-treat analysis versus per protocol analysis**

*Intention-to-treat (ITT) analysis:* Per definition, ITT analysis includes all randomised children. It generally is the preferred strategy for data analysis in superiority trials (objective 2 above) because a) it tends to avoid over-optimistic estimates of effect in real-life conditions, because non-compliers included in the ITT set will generally reduce the estimated treatment effect;[8] b) ITT analysis with multiple imputation yields valid results when missingness of data is random. Most trials aim to estimate the effects of allocating an intervention in real-life conditions, not the effects in the subgroup of the participants who adhere to it.

In a non-inferiority trial, however, intention-to-treat analysis is generally not conservative because protocol violation and non-adherence to treatment may cause the results of the treatment groups to appear similar [9].

*Per protocol analysis:* Per protocol analysis is restricted to participants who have adhered closely to what is prescribed in the study protocol in the terms of eligibility, interventions, and outcome assessment. It does not show the practical value of the experimental intervention, but rather envisages determining the biological effect of the intervention that can be obtained under ideal circumstances, with participants who adhere to trial instructions. However, missing outcome data due to attrition (drop-out) during the study or exclusions from the analysis raise the possibility that effect estimates obtained by per protocol analysis is biased. Per protocol analysis may also raise concerns about data manipulation.

In our study, we will include children in per protocol analysis who received at least one dose of home fortification, with exclusion of those not meeting inclusion criteria, poorly adhered to intervention, crossed over between intervention groups or ingested iron-containing preparations acquired outside the trial, and excluding those with missing outcome data. We will define adherence as the number of days that home fortificants have been made available relative to the scheduled 30-day intervention period, with availability indicated by the electronic device for storage of home fortificants having been opened. Poor adherence will be defined as adherence < 80% (23 days). This threshold is somewhat arbitrary, but it has been used in most published studies on medication adherence [10,11] and we believe that adherence above this threshold to be associated with improved iron status. Group adherence will be reported as the proportion of participants for whom home fortificants were available ≥80% (≥24 days).

*Relative importance of intention-to-treat analysis and per protocol analysis:* We conceived the SEICK trial primarily to be an explanatory trial (i.e. to assess intervention effects under optimal conditions) rather than a pragmatic trial (i.e. to assess intervention effects under real-life conditions). As per recommendations [12] we will pursue the primary (non-inferiority) objective by comparing results obtained by both intention-to-treat analysis and per protocol analysis. Non-inferiority will be accepted only if efficacy (objective #2), assay sensitivity (objective #2) and non-inferiority (objective #1) have all been shown. In our trial report, we will include results of the per protocol analysis in the main text, and results of the intention-to-treat analysis as supplementary material.

1. **Handling of outliers and missing data**

Outliers will be identified by examining a) ranges of continuous variables; b) frequency tables of categorical variables; c) visual inspection of scatter plots of pairs of continuous variables. Outliers will be dropped only if it is obvious that they are due to incorrectly entered or measured data.

Reasons for missing outcome data will be given where possible, coded and reported quantitatively as either a) withdrawal of consent; b) adverse events or withdrawn for medical reasons (reasons specified); c) no show for follow-up visit(s); d) moved away from the study area; e) refused intervention; f) refused to give human tissue samples; g) excluded from analysis due to not meeting inclusion criteria; h) excluded from analysis due to poor adherence to intervention; i) excluded from analysis due to crossing over between intervention groups; j) excluded from analysis due to taking iron-containing preparations acquired outside the trial; k) other reasons (specified).

For ITT analysis, missing data will be replaced under a missing-at-random assumption by multiple imputation (SPSS, ‘automatic’ imputation method; 20 iterations), with log-transformed variables as necessary to normalize distributions. Imputations will be done separately for each of the three intervention groups, with datasets derived with these imputed values being merged to allow subsequent analysis. All variables used in regression models will be included in the imputation model; these will include both baseline factors and outcomes. A list of these variables will be reported as supplementary material.

1. **Participant flow**

Figure 3 shows the format for presenting the flow of children during the four main stages of the trial (enrolment, allocation, follow-up and analysis). For children who were excluded before randomisation, reasons will be given where possible, coded and reported quantitatively as either a) no show; b) refused to participate; c) no written informed consent obtained; d) unlikely to stick to protocol; e) ineligible (with reasons specified if possible); f) medical conditions (with reasons specified if possible); g) other reasons; h) not known.

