**Figure S3: Flow of study participant (incomplete)**

1. **Description of group characteristics at baseline**

For continuous variables, we will visually inspect histograms to assess whether they are normally distributed within intervention groups, with log-transformation of variables with a lognormal distribution. Population characteristics (Table 1) will be reported by intervention group as proportions, means (SD), geometric mean (geometric SD), and median (25th- and 75th percentiles) as appropriate, with corresponding group size. We will not test for group differences for reasons given by Assmann et al. [13].

Table S1: Description of baseline characteristics

| Variable | Type | Units/categories |
| --- | --- | --- |
| Age | Continuous | months |
| Age class | Binary | 12-23 months, 24-36 months |
| Sex | Binary | %males : %females |
| Height-for-age z-score | Continuous | SD |
| Weight-for-height z-score | Continuous | SD |
| Weight-for-age z-score | Continuous | SD |
| Haemoglobin concentration | Continuous | g/L |
| Anaemia status | Ordinal | *Severe to moderate anaemia:* haemoglobin concentration <89g/L; *mild anaemia:* haemoglobin concentration 90-109g/L; *non-anaemic:* haemoglobin concentration ≥110g/L |
| Plasma ferritin concentration | Continuous | μg/L |
| Iron status | Nominal | *Deficient:* plasma ferritin concentration <12 µg/L regardless of presence or absence of infection or inflammation; *replete:* plasma ferritin concentration ≥12 µg/L in the absence of infection or inflammation; *uncertain:* plasma ferritin concentration ≥12 µg/L in the presence of infection or inflammation |
| Plasma soluble transferrin receptor concentration | Continuous | mg/L |
| Plasma C-reactive protein concentration | Continuous | mg/L |
| Plasma *α*_1_-acid glycoprotein concentration | Continuous | mg/L |
| Inflammation | Binary | Plasma concentrations of C -reactive protein (CRP) > 5mg/L and/or α_1_-acid glycoprotein (AGP) > 1g/L |
| Whole blood ZPP concentration | Continuous | μmol/mol haem |
| Erythrocyte ZPP concentration | Continuous | μmol/mol haem |
| *Plasmodium* parasite density (asexual and sexual forms) | Continuous | µL^-1^ |
| *Plasmodium* infection, by rapid dipstick tests | Nominal | No infection; *P. falciparum* (by HRP2 or *P. falciparum*-specific pLDH), other human *Plasmodium* spp. (by pLDH), mixed infection |
| Urinary hepcidin concentration * | Continuous | nmol/mmol creatinine |
| Plasma folate concentration * | Continuous | nmol/L |

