1. *Adjustment* *for selected baseline variables:* Biased effect estimates would occur if there are group imbalances in baseline factors that are prognostic for outcome. For baseline factors that are known to be strongly, or at least moderately, associated with the primary outcome, or for which there is a strong biological rationale for such an association, i.e. iron status, plasma soluble transferrin receptor concentration, and age, we will evaluate the role of such bias using stratified analysis and directly by multiple linear regression models. We also expect haemoglobin concentration at baseline to be prognostic for outcome but, because this will already be accounted for by adjusting for study design. In stratified analysis, we will estimate intervention effects in subgroups formed by these baseline factors (for iron status: see definition in Table 1; plasma soluble transferrin receptor concentration dichotomised with the median as cut-off value; and age in classes of children aged 12-23 months and 24-30 months) to allow an assessment of the validity of model assumptions. In the regression models, we will compare effect estimates with and without adjustment by baseline factors (plasma concentrations of ferritin and soluble transferrin receptor and age; as continuous variables). In the interpretation of data, we will give priority to the unadjusted effect, unless the adjusted effect is markedly different (>15%), in which case the adjusted effect will be considered the primary analysis.

*Subgroup analysis:* Because iron absorption is known to depend on iron status, we will consider proxy markers for iron status (haemoglobin concentration, plasma concentrations of ferritin and soluble transferrin) at baseline as potential modifiers for intervention effects.

Stratified analysis will be used to measure effect sizes within subgroups. Evidence for group differences in intervention effects will be formally investigated in a multiple regression model with main effects (for baseline factors and the intervention) and multiplicative interaction terms.

To define subgroups, baseline factors will be categorized (haemoglobin concentration class <100 g/L and ≥100 g/L; iron status [see classification above] and plasma soluble transferrin receptor concentration [dichotomised, with the median as threshold]). For iron status, we will restrict the analysis to a comparison of iron-deficient and iron-replete subgroups.

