Categorisation of baseline factors has the advantage that results can be conveniently presented in a forest plot. It has the disadvantage, however, that the precision of the interaction depends on the number and position of the cut-off values used to categorise baseline factors [16]. We will also explore interactions with baseline factors as continuous covariates, using fractional polynomials [16]. Such a strategy is more powerful, especially at towards extreme ends of the covariate distribution where limited numbers of observations generally preclude detection of interaction, and it may reveal more about the nature of possible interactions. We will inspect scattergrams and conduct sensitivity analysis as needed to examine the influence of possible outliers on results.

Results of subgroup analyses will be interpreted cautiously for reasons reported elsewhere [13].

1. *Intention-to-treat analysis:* For binary outcomes, pooled estimates from multiple iterations may result in non-integer values. This precludes computation of confidence intervals for differences in proportions, and may be counterintuitive to readers not well versed in multiple imputation techniques. To handle this problem, we will calculate differences in means under the assumption of binary outcome variables having a Bernoulli distribution. Pooled chi-squared statistics for cross-tabulated data and associated p-values will be calculated as described by Van Buuren (2012), thus the p-values obtained are only crude estimates of the true values [17].
2. *Paired comparisons of iron groups with placebo (objective 2):* This analysis will be done as for the comparison between iron groups (see above). Superiority will be established if no effect is excluded from the 95% CI.
3. **Analysis of secondary outcomes (objectives 1b and 2)**

To assess intervention effects, we will conduct all three possible paired comparisons between the intervention groups. We will use plasma ferritin concentration as an outcome indicator of iron status, and soluble transferrin receptor as an outcome indicator of the iron demand by the erythrocytes (both measured at the end of the 30-day intervention period). We will conduct analysis with and without adjustment for baseline factors, as well as intention-to-treat analysis (see methods above).

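### Day-30 P. falciparum infection may include infection already present at entry, yet baseline infection, which is collected, is in no stated model for objective 1e

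*SAP*

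**What the plan says.** **Outcome.** Objective 1e (SAP, Trial objectives) is P. falciparum "infection at the end of the fortification period as indicated by whole blood density of asexual parasites or the presence of antigenemia". Objective 2 repeats it for iron versus placebo through "The indicators listed under objective 1a-f". The objectives set aside are others: "Objectives 1c, 1d, 4 and 5 are conditional to sufficient resources still being found". Objective 1e therefore remains in the plan.

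**Baseline data.** Table S1 lists Plasmodium "parasite density (asexual and sexual forms") and Plasmodium "infection, by rapid dipstick tests". Neither row carries the funds-permitting mark that some other rows have.

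**Design.** Randomisation (Study type and key design features) uses "strata defined by baseline haemoglobin concentration class (<100 g/L and ≥100 g/L"). Infection is not a stratum.

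**Adjustment.** In the section on the primary outcome, factors are selected for their association with haemoglobin, and the regression covariates are "plasma concentrations of ferritin and soluble transferrin receptor and age; as continuous variables". The section on secondary outcomes is headed for objectives 1b and 2 and says: "We will conduct analysis with and without adjustment for baseline factors, as well as intention-to-treat analysis (see methods above"). Its outcome-specific text covers only ferritin and soluble transferrin receptor, for which end-of-intervention CRP and AGP are added. No model for infection is described, and baseline Plasmodium status enters no stated model.

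**The concern.** The outcome is a state at day 30 and is not restricted to new infection. If some children were parasitaemic or antigen-positive at entry and remained so, their day-30 result would partly reflect what they brought into the trial. Baseline infection would then predict the outcome, much as baseline haemoglobin predicts final haemoglobin. For haemoglobin the SAP deals with this by stratifying and adjusting, and it gives precision as a reason. For infection it does neither, although the baseline value is available.

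Infection is the only malaria outcome among the objectives, and the sample size was set for haemoglobin. Precision for the infection comparison is therefore whatever the analysis can recover. Ignoring a strong baseline predictor would widen the interval and leave the estimate exposed to any chance imbalance in infection at entry.

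**Working it through.** **Inputs from the SAP.** The target is 108 children per arm, and binary effects are reported as differences in proportions with 95% CIs. The SAP gives no figure for infection to reproduce. The 108 was set for haemoglobin. With the 4.7 g/L margin, a true difference of 0 and one-sided 2.5%, it implies an SD of about 12.3 g/L at 80% power or 10.65 g/L at 90%. The SAP states neither SD nor power, so 108 is taken as given.

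**Inputs assumed.** b is the proportion infected at baseline. p1 and p0 are the proportions positive at day 30 among children infected and uninfected at baseline. None is in the SAP, so ranges are used. Both arms are given the same rates, and all 108 per arm are assumed to have outcome data. The arithmetic covers the positive/negative outcome only, not density as a continuous outcome.

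**Formulas**
- Day-30 prevalence: q = b·p1 + (1−b)·p0
- Unadjusted 95% half-width: 1.96·√[2q(1−q)/108]
- Share of variance explained: R² = b(1−b)(p1−p0)² / [q(1−q)]
- Adjusted half-width: unadjusted × √(1−R²)

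**Middle case** (b = 30%, p1 = 70%, p0 = 12%)
- q = 0.210 + 0.084 = 0.294, so q(1−q) = 0.2076
- R² = 0.21 × 0.58² / 0.2076 = 0.34
- Unadjusted half-width = 1.96 × √(2 × 0.2076/108) = 12.2 points
- Adjusted half-width = 12.2 × √0.66 = 9.9 points, equivalent to 1/0.66 = 1.5 times the children per arm

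**Range for b 20-40%, p1 50-80%, p0 10-15%**
- Smallest gain (20%, 50%, 15%): q = 0.22; R² = 0.16 × 0.1225/0.1716 = 0.114; narrowing 1 − √0.886 = 6%
- Largest gain (40%, 80%, 10%): q = 0.38; R² = 0.24 × 0.49/0.2356 = 0.499; narrowing 1 − √0.501 = 29%

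**How the gain depends on carry-over** (p0 = 10%). The last column is the simulated ratio of adjusted to unadjusted variance from 40,000 trials, using a stratum-weighted risk difference.

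| b | p1 | R² | Half-width, points | Simulated ratio |
|---|---|---|---|---|
| 30% | 10% (none) | 0 | 8.0 → 8.0 | 1.005 |
| 30% | 30% | 0.06 | 9.8 → 9.5 | not run |
| 30% | 50% | 0.20 | 11.0 → 9.9 | 0.80 |
| 30% | 80% | 0.48 | 12.3 → 8.9 | 0.52 |

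**Chance imbalance.** The 95% range of the between-arm difference in baseline infection is ±1.96·√[2b(1−b)/108]. At b = 30% this is ±12.2 points. An imbalance at that edge moves the unadjusted day-30 difference by 12.2 × (p1−p0). With p0 = 10% the shift is 2.4 points (p1 = 30%), 4.9 (p1 = 50%) or 8.6 (p1 = 80%), and nil without carry-over. Averaged over randomisations, the simulated unadjusted difference was zero to three decimals.

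**The case against.** The strongest objection is that carry-over is not shown. Recording infection at baseline does not prove that infected children were enrolled, or that their infection was still present at the first dose. The SAP gives neither the eligibility rules nor the handling of baseline infections, and the protocol is not at hand. A reader might infer that the day-30 outcome does contain earlier infections. The documents support only that it may. This stands, and it is why the gain has to be stated from nil upwards.

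Second, a reader might infer that the SAP has chosen ferritin, soluble transferrin receptor and age as the covariates for infection. It has not clearly done so. That list was written for haemoglobin, and the heading of the secondary-outcome section omits 1e except through objective 2. This also stands, but it does not rescue the plan, because baseline infection is absent on either reading.

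Third, randomisation makes the unadjusted difference unbiased, and its CI already allows for chance imbalance. For haemoglobin the SAP deliberately gives the unadjusted effect priority unless adjustment changes it by more than 15%. The statistical part is correct, so describing the gap as systematic bias would be wrong. What remains is lost precision and exposure to whatever imbalance actually occurs. The SAP's own section on the primary outcome treats imbalance in prognostic factors as worth adjusting for.

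**Conclusion.** The point holds as one of precision and conditional imbalance on a secondary objective. It is not a finding of bias. The SAP leaves an already collected and potentially strong predictor out of every stated model for objective 1e, and it specifies no infection model.

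Under the assumed rates, baseline infection explains about 11-50% of outcome variance and adjustment narrows the 95% CI by about 6-29%, with ±12.2 falling to ±9.9 points in the middle case. All three rates are assumptions. If few children were infected at entry, or if day-30 risk did not depend on baseline status, the gain would be small or nil. Adjustment would then cost almost nothing (simulated variance ratio 1.005). A possible benefit against a negligible cost justifies the change without settling how much carry-over there was.

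**What to change.** Add a short analysis paragraph for objective 1e and its placebo comparisons under objective 2:

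- **Main estimate:** the difference in proportions, adjusted for baseline Plasmodium infection and the haemoglobin stratum. For antigenaemia, use the baseline dipstick result as positive/negative, and state how the other-species and mixed categories are grouped.
- **Density outcomes:** use a baseline parasitaemia indicator plus log density among positives, because the log is undefined at zero. Table S1 lists baseline density for asexual and sexual forms, whereas the outcome is asexual, so use asexual P. falciparum counts if they are available.
- **Alongside:** report the unadjusted difference.
- **Supportive:** compare day-30 infection among children negative at baseline, which bears more directly on infection acquired during fortification.

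The cost is SAP wording only. Both baseline measures are already listed in Table S1, and no children or procedures are added. The covariates should be fixed before the randomisation code is broken, so that their choice cannot follow the results.

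### The ITT imputation model does not commit to using adherence or outside iron intake, so children who stopped the sachets and have no end-of-intervention haemoglobin would be imputed mostly from adherent children in their arm

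*SAP*

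**What the plan says.** Under the heading on outliers and missing data, the SAP says that for ITT "missing data will be replaced under a missing-at-random assumption by multiple imputation". It adds that "Imputations will be done separately for each of the three intervention groups", with the datasets then merged. The content of the model is set by one rule: "All variables used in regression models will be included in the imputation model; these will include both baseline factors and outcomes". The final list is deferred: "A list of these variables will be reported as supplementary material".

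The same section codes the reasons for missing outcome data. They include withdrawal of consent, withdrawal for adverse events or medical reasons, and "e) refused intervention; f) refused to give human tissue samples". The list also holds analysis exclusions (codes g to j), such as "h) excluded from analysis due to poor adherence to intervention".

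The section on ITT versus per protocol analysis measures adherence by days of availability, "with availability indicated by the electronic device for storage of home fortificants having been opened". It uses adherence and outside iron preparations to define the per protocol set. It prefers ITT for the superiority comparisons partly "because non-compliers included in the ITT set will generally reduce the estimated treatment effect".

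**The concern.** Missing-at-random is credible only if the imputation model holds the variables that drive both missingness and outcome. Here one such variable is evident. Refusing the intervention, withdrawing consent and being withdrawn for medical reasons all go with stopping the sachets, and the SAP itself expects good adherence to go with better iron status. Adherence is recorded electronically, but nothing commits the analyst to putting it in the imputation model.

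Without it, a child in an iron arm who stopped and was not measured is treated like the average measured child of that arm, most of whom took the product. That works against the SAP's own reason for ITT, which is that non-compliers stay in and dilute the effect.

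Two things are at stake. Non-inferiority is accepted only if efficacy and assay sensitivity, both contrasts with placebo, are also shown. The primary objective also rests on comparing ITT with per protocol, and that comparison tells less if imputation moves ITT towards per protocol. The SAP names no analysis that departs from missing-at-random.

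**Working it through.** **Does any named regression bring adherence in?** For the primary outcome, the covariates are baseline ferritin, soluble transferrin receptor and age, plus the haemoglobin stratum through the design. For the secondary outcomes, C-reactive protein and α1-acid glycoprotein at the end of the intervention are added. Neither adherence nor outside iron appears. End-of-intervention ferritin, transferrin receptor and inflammation markers qualify as regression variables, but they help little in a child for whom they are missing along with haemoglobin.

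**The SAP's own figures.** It states no missingness rate, refusal rate or adherence rate, so there is no planned figure to reproduce. Only the illustrative effect comes from the SAP: 9.3 g/L, the minimum anticipated effect of 12.5 mg ferrous fumarate (M1). All other inputs below are assumptions.

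**First illustration.** Let m be the share of an iron arm with missing haemoglobin and k the share of the effect kept by non-adherent children. Assume non-adherence of 80% among missing and 15% among observed children.

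- Effect imputed to missing children: 9.3 × [1 − 0.15(1 − k)], which is 7.9 g/L at k = 0 and 8.6 g/L at k = 0.5.
- Effect they truly have: 9.3 × [1 − 0.80(1 − k)], which is 1.9 g/L at k = 0 and 5.6 g/L at k = 0.5.
- Overstatement of the arm's effect: m × (0.80 − 0.15) × 9.3 × (1 − k).

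| m | k = 0.5 | k = 0 |
|---|---|---|
| 5% | 0.15 g/L | 0.30 g/L |
| 10% | 0.30 g/L | 0.60 g/L |
| 20% | 0.60 g/L | 1.21 g/L |

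The largest value is 1.21/9.3 = 13% of M1.

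**Second illustration, with different assumptions.** Let a share u of an iron arm stop and get no effect, let a share q of those be missing, and let everyone else be measured with the effect of 9.3 g/L. The true ITT effect is 9.3(1 − u). Imputation without adherence gives 9.3(1 − u)/(1 − uq). The overstatement is the difference:

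| u | q = 25% | q = 50% | q = 100% |
|---|---|---|---|
| 5% | 0.11 g/L | 0.23 g/L | 0.46 g/L |
| 10% | 0.21 g/L | 0.44 g/L | 0.93 g/L |
| 20% | 0.39 g/L | 0.83 g/L | 1.86 g/L |

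**Does adding adherence help?** A simulation of 400,000 children per scenario, with q = 50%, gave:

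| u | True effect | Imputed without adherence | Imputed with adherence |
|---|---|---|---|
| 10% | 8.36 g/L | 8.80 g/L | 8.36 g/L |
| 20% | 7.46 g/L | 8.29 g/L | 7.47 g/L |

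At q = 100% no stopper is measured, so an adherence term cannot identify their mean.

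**The contrast between the iron arms.** Take all stoppers as missing.

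- Equal full effects and equal stopping: no shift.
- Equal full effects, 10% stopping on NaFeEDTA and 5% on fumarate: 0.46 g/L towards non-inferiority. With the rates reversed, the shift is 0.46 g/L the other way.
- NaFeEDTA effect lower by 4.7 g/L and 10% stopping in both arms: the true difference of −4.23 is estimated as −4.70, a shift of 0.47 g/L away from non-inferiority.

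**The case against.** The best defence is that the sentence on the imputation model sets a minimum. It does not say that only regression variables may enter, the list is left open, outcomes are included, and adherence is a listed comparison under the first objective. This stands. A reader might infer that the SAP excludes adherence, but the text shows only that it does not commit to including it.

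A reader might also infer that stoppers are imputed with the full effect of the product. That does not follow. ITT keeps every randomised child, so measured non-adherers inform the imputation. On the first illustration's inputs the imputed effect is 85% (7.9/9.3) to 93% (8.6/9.3) of the full effect. It reaches 100% only if every non-adherer is missing. One ambiguity could bring this about: poor adherence, crossing over and outside iron are coded as reasons for missing outcome data. If those children's measured values were blanked and imputed for ITT, the full-effect reading would nearly hold. The SAP does not say that this will be done.

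Nor is imputing within arm a fault. It preserves arm-specific relations and the planned interactions.

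The rates are assumed, and the 80% figure drives the first illustration. Some listed reasons, such as moving away or not attending, need not reflect stopping. ITT results are also supplementary in the report. These points limit the size and weight of the concern. They do not remove it, because ITT is one of the two analyses compared for the primary conclusion, and a better model needs only data that the per protocol definition already requires.

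**Conclusion.** The point holds as a moderate weakness. The SAP does not commit to the recorded variables that would make missing-at-random more plausible, and it has no sensitivity analysis for departures from it. The expected direction is overstatement of the ITT contrasts of iron with placebo, and so of efficacy and assay sensitivity, with ITT drawn towards per protocol. On the first set of assumptions the size is about 0.3 to 0.6 g/L with 10% missing and 0.6 to 1.2 g/L with 20% missing. The upper value needs 20% missing, 80% of those non-adherent and no residual effect, all together.

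A reader might conclude that the primary iron-iron contrast is biased towards non-inferiority. The SAP does not support that. The shift is nil with equal stopping and equal effects, and otherwise it can go either way.

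**What to change.** Keep imputation within arm, and add to the section on outliers and missing data:

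1. The number of days on which the electronic device was opened, and outside iron intake (yes/no), enter the imputation model as auxiliary variables in each arm. The first is already defined. The second is named only as a per protocol exclusion and needs a short definition.
2. Measured haemoglobin values of children under codes g to j are never set to missing for the ITT analysis.
3. A delta or reference-based sensitivity analysis is run for children with missing haemoglobin, because auxiliary variables cannot identify the mean if every stopper is missing. Its shift or reference arm should be fixed before unblinding.

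The cost is small: two variables in the imputation command and one further analysis. Where the device record is itself missing, adherence must be imputed too, so intervals may widen slightly.
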